## Abstract

•

**[name]:**

**[name] [name]:**

**[name] and [name] [name]:**

**[name]:**

## Specifications table

**Table utbl0001:** 

**Subject area**	Nursing and Medicine
**More specific subject area**	Community-based care for chronic diseases (Diabetes and Hypertension)
Name of protocol	Community-Based intervention (CBI) for Individuals with Coexisting Diabetes and Hypertension
**Reagents/tools / Instruments**	- Sociodemographic proforma and Clinical Profile Form - Digital Sphygmomanometer (BP measurement) - Standardized Glucometer (Random Blood Sugar Test) - Modified Diabetes and Hypertension Health Literacy Scale - 8-item Morisky Medication Adherence Scale (MMAS-8) - Modified Quality of Life Questionnaire
**Experimental design**	Randomized controlled trials (block randomization) with 1:1 allocation between intervention and control groups. **Intervention group:** Participants will receive the CBI, including: [1] pre-intervention orientation and baseline assessment, [2] yoga-based lifestyle modification and nurse-led counseling (6 days/week for 6 weeks), and [3] home-based monitoring and follow-up reinforcement. **Control group:** Participants will continue standard care and receive informational booklets on yoga and dietary management after intervention completion. Follow-up assessments will be conducted at 2 months, 3 months, and 6 months.
Trail registration	Registered in Clinical Trial Registry of India (CTRI/2024/08/071,775)
Ethics	Approved by Institutional Ethics Committee (IEC) of Institute of Medical Sciences and SUM Hospital, Siksha ‘O’ Anusandhan, Bhubaneswar, Odisha, India (Reference no: IEC/IMS.SH/SOA/2022/433). The study will adhere to the Declaration of Helsinki, ensuring voluntary participation, confidentiality, and participant safety.
Value of the protocol	1) Provides evidence on the effectiveness of a structured community-based intervention for patients with coexisting diabetes and hypertension. 2) Facilitates patient-centered care by integrating yoga, education, and home monitoring into routine treatment. 3) Offers insights for developing scalable interventions in urban slum populations to improve medication adherence, clinical outcomes, and quality of life.

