## Intervention group

Participants in the intervention group will receive a structured Community-Based Intervention (CBI) in addition to standard medical care. The CBI is designed to provide holistic care by integrating education, yoga-based lifestyle modification, and home-based monitoring. The intervention will be delivered in groups of 8–10 participants, led by the same trained nurse facilitator throughout the study, with support from a certified yoga instructor for yoga sessions. The complete intervention will span 6 weeks, with sessions conducted six days per week.

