### Home-Based monitoring and follow-up reinforcement

To strengthen continuity of care, participants will be trained in home-based monitoring of blood pressure and blood glucose and will maintain a lifestyle diary documenting daily yoga practice, diet, and medication adherence. The nurse will provide follow-up reinforcement through weekly contacts in the first month and biweekly thereafter, conducted via home visits or telephone calls. During these interactions, the nurse will review self-monitoring records, reinforce educational content, troubleshoot difficulties, and provide motivational support. Participants who show poor adherence or worsening clinical indicators will receive additional counseling and relate to peer support strategies to encourage engagement and compliance.

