## Control arm

Participants randomized to the control group will continue to receive routine medical care as prescribed by their physician. This care will include regular consultations with a physician, prescribed medications, routine monitoring of blood pressure and blood glucose, and general guidance on diet, physical activity, and lifestyle management. The control group will not receive any additional interventions, such as educational sessions, yoga-based activities, or nurse-led counseling. This design provides a clear comparator for assessing the effectiveness of the structured community-based intervention delivered to the experimental group.

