## Data collection plan and management

The initial survey will be conducted within selected urban slum communities to identify individuals diagnosed with both diabetes mellitus and hypertension. Eligible participants will be approached at their households to ensure accessibility and convenience. Trained community health workers, under the supervision of the research team, will carry out the survey following standardized procedures to ensure consistency and accuracy. After screening for eligibility and obtaining written informed consent, baseline data will be collected using structured interviews. Once baseline assessments are completed, participants will be allocated to either the intervention or control group using a computer-generated block randomization procedure. Follow-up data will be collected at multiple time points: baseline, 2 months, 3 months, and 6 months to evaluate both short- and mid-term outcomes.

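### As written, controls may be given yoga and diet booklets from week 6, before the 2-, 3- and 6-month assessments, although the control-arm text rules out additional interventions

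*Protocol article*

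**What the plan says.** Four places in the protocol article bear on this.

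- **Specifications table, Experimental design:** controls continue standard care and "receive informational booklets on yoga and dietary management after intervention completion". The next sentence reads "Follow-up assessments will be conducted at 2 months, 3 months, and 6 months".
- **Intervention group:** "The complete intervention will span 6 weeks, with sessions conducted six days per week".
- **Home-Based monitoring and follow-up reinforcement:** nurse contacts are "weekly contacts in the first month and biweekly thereafter". No end is given.
- **Control arm:** "The control group will not receive any additional interventions, such as educational sessions, yoga-based activities, or nurse-led counseling". Booklets are not mentioned, and the section concludes: "This design provides a clear comparator for assessing the effectiveness of the structured community-based intervention delivered to the experimental group".

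The Data collection plan and management section repeats the schedule: "Follow-up data will be collected at multiple time points: baseline, 2 months, 3 months, and 6 months". The outcome sections use the same times for blood pressure, blood glucose, health literacy, medication adherence and quality of life.

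**The concern.** The booklets cover two named components of the intervention, yoga and diet. If completion means the end of the 6-week programme, controls may hold them before the first follow-up visit and at every later one. No assessment falls between baseline and week 6, so on that reading no post-baseline comparison is clearly free of them.

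Health literacy is the most exposed outcome. The Aim of the study section places it in the primary aim, and its scale tests understanding of diet, physical activity and self-care, which printed material can convey directly. Improvement among controls would shrink the difference between arms, and a null result would then be hard to interpret.

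The two descriptions of the control arm also disagree. One adds study-supplied material to routine care, and the other says nothing is added. A reader cannot tell from them what controls receive, or when.

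**Working it through.** **Step 1: timeline.** Inputs are an intervention of 6 weeks (Intervention group) and follow-up at 2, 3 and 6 months (Specifications table; Data collection plan and management). One month is 365.25 / 12 / 7 = 4.348 weeks. I assume the follow-up clock and the intervention start together, since the protocol does not define the starting point.

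| Visit | Week | Weeks after week 6 |
|---|---|---|
| 2 months | 8.7 | 2.7 |
| 3 months | 13.0 | 7.0 |
| 6 months | 26.1 | 20.1 |

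All three visits fall after week 6. If the programme began more than about 2.7 weeks after baseline, the 2-month visit would come before its end. For the 3-month visit the delay would have to exceed about 7 weeks.

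**Step 2: is there a rule that holds the booklets back?** The Specifications table ties them only to the end of the intervention. The Control arm, Data collection plan and management, and Follow-Up and data collection procedures sections do not mention them. No rule was found.

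**Step 3: when does the intervention end?** The Intervention group section says 6 weeks for the whole. The Specifications table lists home monitoring and reinforcement as the third component and attaches the 6 weeks only to the second, yoga and counseling. The reinforcement section gives contacts a frequency but no last date. The end is therefore week 6 on one passage and undetermined on the others.

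**Step 4: the plan's own sample size.** The Sample size section gives 0.74 (read as an SD, which reproduces the plan's figure), a difference of 0.40, and z values of 1.96 and 0.84.

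n = 2 × 0.74² × (1.96 + 0.84)² / 0.40² = 2 × 0.5476 × 7.84 / 0.16 = 53.7, so 54 per group.

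With 10% attrition, 54 / 0.90 = 60 per group. Both figures reproduce.

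**Step 5: what dilution would do (illustration only).** Suppose the booklets remove a fraction f of the 0.40 difference. The protocol gives no value for f. With 54 analysed per group, the standard error is 0.74 × √(2/54) = 0.1424, and power ≈ Φ(0.40 × (1 − f) / 0.1424 − 1.96).

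| f (assumed) | Difference | Power |
|---|---|---|
| 0% | 0.40 | 80.2% |
| 10% | 0.36 | 71.5% |
| 20% | 0.32 | 61.3% |
| 30% | 0.28 | 50.2% |

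The increase to 60 per group covers only the planned attrition, so there is no reserve against dilution.

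**The case against.** **The date is inferred.** The table's phrase sets an earliest time, not a hand-out day. The authors may have meant a courtesy hand-out once all outcomes are in, and that reading would reconcile the table with the Control arm section. This stands as a limit on the claim: early exposure is permitted, not shown to be planned. It does not remove the problem, because no passage states the later date and staff could properly act at week 6.

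**Completion may be later.** If everything stopped at week 6, the biweekly phase after the first month would last about two weeks, or roughly one contact. That suggests reinforcement was meant to run on. This is a fair point, but it conflicts with the 6-week statement and makes the hand-out date less certain.

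**A reader might infer that the trial no longer compares the intervention with standard care.** The protocol does not support that. The intervention is supervised group yoga six days a week, weekly nurse coaching, home monitoring, a diary and nurse contacts. A booklet is far weaker, and routine care already includes general guidance on diet and activity. A meaningful contrast would remain, and dilution would not create a false positive.

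**A reader might take the power figures as an estimate of the loss.** They are not. The fractions are assumed, the Sample size section does not say which outcome 0.40 and 0.74 describe, and a constant loss at every visit is a simplification, since the 2-month visit could come under three weeks after the earliest hand-out.

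**An article may leave an exact hand-out date to the full protocol.** That would answer a missing date. It does not answer a stated rule that allows exposure before measurement, or two accounts of the control arm that differ.

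**Conclusion.** The concern holds as a matter of what the text permits. Controls may receive the booklets from week 6, before the 2-, 3- and 6-month assessments, and nothing delays them until outcomes are measured. This conflicts with the statement that controls receive no additional interventions, and the undefined end of the nurse contacts leaves the trigger for hand-out unclear.

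Any bias would be towards no difference, most plausibly for health literacy. Its size cannot be derived from the protocol; the fall in power to about 72%, 61% or 50% applies only under assumed dilution of 10%, 20% or 30%. The timeline rests on the 6-week definition and on a follow-up clock that starts with the intervention. The point should be settled before any booklet is distributed, because exposure that has already occurred cannot be undone in the analysis.

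**What to change.** Reconcile the Specifications table with the Intervention group, Home-Based monitoring and follow-up reinforcement, and Control arm sections:

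1. State, in both the table and the Control arm section, that each control participant receives the booklets only after their own 6-month assessment.
2. State when the intervention ends, including the nurse contacts, so that the 6-week figure and the biweekly contacts agree.
3. If earlier hand-out is kept, describe the comparator throughout as standard care plus booklet, and give the hand-out time relative to the 2-, 3- and 6-month visits.

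The cost is a few sentences and a later hand-out of the same material. Controls would wait a few months longer for it. With the booklets held until after the last assessment, the planned 80% power at 54 per group (60 enrolled) is unaffected by them.

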## Background

Diabetes and hypertension are two of the most prevalent noncommunicable diseases (NCDs) worldwide and are leading contributors to morbidity and mortality [1,2]. Diabetes is characterized by persistent hyperglycemia resulting from insufficient insulin secretion or impaired insulin utilization, which over time causes damage to multiple organ systems [3,4]. Hypertension, defined as systolic blood pressure ≥140 mmHg or diastolic blood pressure ≥90 mmHg or current use of antihypertensive medication, increases the risk of cardiovascular disease, stroke, kidney failure, and premature mortality [5]. Globally, the burden of these conditions is rapidly escalating, with more than 529 million people living with diabetes in 2021 a figure projected to reach 700 million by 2045 and nearly one billion people affected by hypertension, expected to rise to 1.56 billion by 2025 [6,7]. Recognising this challenge, the World Health Organisation’s Global Action Plan for the Prevention and Control of NCDs has set targets to halt the rise of diabetes and reduce the prevalence of hypertension, while the United Nations’ Sustainable Development Goal 3 aims to reduce premature mortality from NCDs by one-third by 2030 [8].

India carries a disproportionate share of this global burden, with nearly 69.1 million people living with diabetes and hypertension projected to increase by 80 % between 2000 and 2025 [6]. Alarmingly, hypertension is increasingly common among young adults, raising the urgency for preventive interventions. The coexistence of diabetes and hypertension further complicates disease management, as more than 80 % of patients with type 2 diabetes develop hypertension, and approximately one-fifth of hypertensive patients later develop diabetes [9]. Their shared pathophysiological mechanisms, including insulin resistance, endothelial dysfunction, and obesity, amplify the risk of complications such as atherosclerosis, nephropathy, retinopathy, and cardiovascular disease, ultimately leading to high healthcare costs and adverse socioeconomic impacts [10].

Addressing this double burden requires strategies beyond pharmacological therapy, with emphasis on lifestyle modifications such as healthy diets, physical activity, stress reduction, and community-based support [11]. Evidence from India and other low- and middle-income countries demonstrates that community-based interventions are effective in improving health outcomes [12]. Programs in Kerala have successfully reduced mean blood pressure and improved awareness and treatment adherence [13], while yoga-based and lifestyle education programs in India and Nepal have shown significant benefits in lowering blood pressure and preventing diabetes. These culturally tailored, low-cost approaches highlight the potential of community-driven interventions to complement clinical care in resource-limited settings [14]. Despite these promising findings, there remains limited evidence from randomized controlled trials (RCTs) that specifically address the combined management of diabetes and hypertension in the Indian context. Most studies have examined these conditions separately, leaving a critical gap in integrated approaches for individuals experiencing both simultaneously. This study seeks to address this gap by implementing and evaluating a structured community-based intervention designed to be implemented among individuals with coexisting diabetes and hypertension.

## Description of protocol

Diabetes and hypertension pose a major global public health challenge, with prevalence steadily increasing, particularly in low- and middle-income countries [12]. Managing these chronic conditions within community settings can be daunting, especially for individuals with limited health literacy, irregular follow-up care, and restricted access to healthcare services [11,12]. Poor treatment adherence, unhealthy lifestyle practices, and inadequate self-care behaviors are key factors contributing to uncontrolled blood pressure and blood sugar levels, ultimately leading to serious complications [16].

A community-based intervention (CBI) integrating yoga, health education, dietary counseling, and regular follow-up support has the potential to improve clinical outcomes and enhance the self-care capacity of patients with diabetes and hypertension. Structured yoga sessions may aid in regulating blood pressure and glucose levels, while targeted health education can strengthen patients’ knowledge and awareness regarding disease management. Dietary guidance supports better nutritional choices, and sustained follow-up encourages treatment adherence and lifestyle modification.

The significance of this trial lies in its potential to provide evidence for integrated chronic disease management, empower patients through improved health literacy, and promote cost-effective strategies that can be scaled within primary healthcare systems. Moreover, the outcomes of this study align with national and global priorities such as the WHO Global Action Plan and the Sustainable Development Goals, thereby contributing to the reduction of premature mortality from NCDs [15]. However, evidence regarding the effectiveness of such interventions remains inconclusive due to variability across studies in terms of patient characteristics, intervention intensity, duration of follow-up, and behavioral support strategies. Therefore, this study protocol outlines a structured and sustainable model of community-based intervention aimed at improving clinical outcomes (blood pressure and blood sugar control), quality of life, health literacy, and medication adherence among adults with diabetes and hypertension living in urban slum settings.

## Aim of the study

The primary aim of the study is to evaluate the effectiveness of a CBI that integrates yoga practices, health education, dietary counseling, regular follow-up, and structured monitoring in improving clinical outcomes (blood pressure and blood sugar control) and health literacy among individuals with coexisting diabetes and hypertension.

## Study design

This study will adopt an RCT design in accordance with the updated SPIRIT 2025 statement guidelines [17]. Eligible participants will be randomly assigned to either the intervention or control group.

## Participants and enrolment

The study will be conducted in selected urban slum communities under the Bhubaneswar Municipal Corporation (BMC), Odisha. The selection of participants will be based on population density and the presence of active Non-Communicable Disease (NCD). In collaboration with local health authorities, the slums will be chosen to ensure adequate representation and logistical feasibility for data collection and intervention delivery. A community health survey will be conducted by a trained researcher in coordination with Accredited Social Health Activists (ASHAs) and Auxiliary Nurse Midwives (ANMs). All data collectors will undergo a structured two-day training program focused on participant screening, ethical considerations, informed consent procedures, and standardized data collection protocols.

The training will be supervised by senior investigators to ensure uniformity and quality assurance. Periodic field monitoring and random checks will be conducted throughout the study to maintain data reliability and adherence to protocol. Eligible participants will include individuals aged between 30 and 60 years who have been previously diagnosed with both diabetes mellitus and hyrtension. Verification of the diagnosis will be carried out through multiple sources, including review of patients’ medical records, confirmation in the NCD registers and the Health Management Information System (HMIS), and validation by the CHOs or healthcare workers based on available clinical documentation. Self-reported cases without medical record confirmation will not be included. All eligible participants will receive a detailed explanation of the study’s purpose, procedures, and potential benefits and risks. Written informed consent will be obtained before enrolment. Following enrolment, participants will be followed up within their community settings throughout the intervention and data collection phases to ensure consistent participation and outcome monitoring.

## Inclusion and exclusion criteria

The inclusion criteria for this study will comprise adults aged between 30–60 years who have been diagnosed with both type 2 diabetes mellitus and hypertension for at least one year. Eligible participants must be residents of the selected community for at least the past six months and are expected to remain there for the next six months. In addition, participants should be receiving treatment from a healthcare provider and must be willing and able to provide informed consent for participation.

Exclusion criteria will include individuals diagnosed with only diabetes or only hypertension without the coexistence of both conditions. Patients with severe complications such as end-stage renal disease, stroke, or advanced cardiovascular disease, as well as those requiring hospitalization, will be excluded. Pregnant women, lactating mothers, and individuals with psychiatric illness, cognitive or physical impairments that limit participation, or those already enrolled in another interventional study will also be excluded. Furthermore, participants who are unwilling or unable to complete follow-up assessments will not be considered.

## Sample size

The sample size was calculated using the formula:$$N=\frac{2\sigma^{2}{\left(Z_{1-\alpha /2}+Z_{1-\beta }\right)}^{2}}{\delta^{2}}$$

Where:*N* = required sample size per groupσ² = pooled standard deviation of the primary outcome measure (assumed as 0.74 from prior studies)δ² = Anticipated difference in mean outcomes between groups (0.40)Z_1−α/2_ = standard normal variate corresponding to a 95 % confidence level (1.96)Z_1−β_ = standard normal variate corresponding to 80 % power (0.84)

By applying these values, the estimated sample size is approximately 54 participants per group. Considering a 10 % attrition rate, the final sample size will be 120 participants (60 in the intervention group and 60 in the control group).

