## Statistical analysis

Data analysis will be performed using SPSS version 28.0. Descriptive statistics, including mean, standard deviation, median, interquartile range, frequency, and percentage, will be calculated to summarize participant characteristics and outcome variables [18]. Inferential statistics, such as independent sample *t*-tests and repeated measures ANOVA, will be used to assess differences in outcomes within and between groups. The choice of parametric or non-parametric tests will depend on the distribution and normality of the data [19].

All analyses will follow the intention-to-treat principle, ensuring that each participant is analyzed in the group to which they were originally assigned, regardless of adherence to the intervention. Missing outcome data will be carefully addressed based on the nature of the missingness. For data missing at random, multiple imputation techniques will be applied. For data not missing at random, alternative approaches, such as last observation carried forward or mean imputation, will be employed. Effectiveness of the intervention will be expressed as differences in proportions with 95 % confidence intervals and 80 % statistical power. Comparisons will be made using appropriate statistical tests with adjustments for multiple comparisons

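### The stated 80% power belongs to a primary outcome that the protocol never names, and it assumes a single unadjusted 5% test although the aim covers several outcomes

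*Protocol article*

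**What the plan says.** All references are to the protocol article.

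- **Sample size.** The inputs are the "pooled standard deviation of the primary outcome measure (assumed as 0.74 from prior studies" and the "Anticipated difference in mean outcomes between groups (0.40". The first is printed beside the symbol σ² and the second beside δ². The normal deviates are the "standard normal variate corresponding to a 95 % confidence level (1.96" and the "standard normal variate corresponding to 80 % power (0.84". The result is that "the estimated sample size is approximately 54 participants per group", followed by "Considering a 10 % attrition rate, the final sample size will be 120 participants", that is, 60 per arm. Neither 0.74 nor 0.40 is given an outcome, a unit, a time point or a citation.
- **Aim of the study.** The primary aim is to assess effectiveness "in improving clinical outcomes (blood pressure and blood sugar control) and health literacy among individuals with coexisting diabetes and hypertension". None of these outcomes is put first.
- **Study outcomes and its subsections.** Clinical outcomes, health literacy, medication adherence and quality of life are listed without ranking. Each is assessed at baseline and at 2, 3 and 6 months.
- **Statistical analysis.** "Comparisons will be made using appropriate statistical tests with adjustments for multiple comparisons". Neither the method of adjustment nor the family of comparisons is stated. The same section names t-tests and repeated measures ANOVA, yet says effectiveness will be reported as differences in proportions.

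**The concern.** A power statement means something only for a named outcome, at a named time, under a named test. Here the calculation relies on a primary outcome that the article does not identify. A reader therefore cannot tell what the 80% refers to, whether 0.40 is a worthwhile difference, or whether 0.74 is a credible SD.

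The health literacy scale shows the difficulty. It is a newly modified 14-item instrument still to be validated, so an SD from prior studies could at best come from a different instrument. Nor is 0.74 easy to read as an SD of blood pressure in mmHg.

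Two further mismatches loosen the link between sample size and analysis. The calculation uses the critical value for one test, while the analysis promises adjustment for several. The calculation also concerns means, while the effect measure concerns proportions.

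What is at stake is the confirmatory test itself. With no primary outcome or time point fixed, the choice of which result counts is left open until the data are in. If the aim's outcomes share the 5%, each has less power than the stated figure at the assumed effect.

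**Working it through.** **Inputs (Sample size section):** SD 0.74; difference 0.40; z = 1.96 and 0.84; 10% attrition; two equal arms.

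**1. Reproduce the plan's figure.**
n = 2 × SD² × (1.96 + 0.84)² / δ² = 2 × 0.5476 × 7.84 / 0.16 = 53.66, rounded up to 54 per arm.
54 / 0.90 = 60 per arm, 120 in total. Both figures reproduce.

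**2. Check the legend.** The printed symbols allow other readings:

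| Reading of 0.74 | Reading of 0.40 | n per arm |
|---|---|---|
| SD | difference | 53.66 → 54 |
| variance | difference | 72.52 → 73 |
| variance | squared difference | 29.01 (about 29) |
| SD | squared difference | 21.47 → 22 |

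Only the first gives 54, so the values were used as an SD and a difference. The squared symbols are a notation slip and do not affect the sample size.

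**3. Power for one test.** The standardised effect is d = 0.40 / 0.74 = 0.5405. With 54 evaluable per arm the expected test statistic is d × √(54/2) = 0.5405 × 5.196 = 2.809. Power = Φ(2.809 − 1.960) = Φ(0.849) = 80.2%. The noncentral t gives 79.5%. If all 60 per arm are evaluable, the normal approximation gives 84.2%.

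**4. Power if the aim's outcomes share the 5%.** The document defines no family or method. The assumptions here are Bonferroni, the same 0.54 SD effect for every outcome, and a two-sample comparison at one visit without baseline adjustment.

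| Outcomes sharing 5% | Two-sided alpha | Critical z | Power, 54 per arm | Power, 60 per arm |
|---|---|---|---|---|
| 1 | 0.05 | 1.960 | 80.2% | 84.2% |
| 2 | 0.025 | 2.241 | 71.5% | 76.4% |
| 3 (blood pressure, glucose, literacy) | 0.0167 | 2.394 | 66.1% | 71.5% |
| 4 (systolic and diastolic separate) | 0.0125 | 2.498 | 62.2% | 67.8% |

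For three outcomes: Φ(2.809 − 2.394) = Φ(0.415) = 66.1%.

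**5. How far baseline adjustment could offset this.** Assume a baseline-to-follow-up correlation of 0.5, a figure the document does not give. The residual variance is then 1 − 0.5² = 0.75 of the original, and the expected statistic becomes 2.809 / √0.75 = 3.243. Power for three outcomes is Φ(3.243 − 2.394) = Φ(0.849), about 80%. The loss in step 4 is therefore conditional on the analysis chosen.

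**The case against.** The strongest reply is that nothing is miscalculated. The formula gives 54, the attrition allowance gives 60, and power is 80% for any single outcome with a true 0.54 SD effect tested at 5%. All of this stands. A reader might infer that the stated power is wrong; the documents do not support that, because the defect is that the figure has no owner.

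The second reply is that the adjustment is not defined. It might apply only to visit contrasts after the repeated measures ANOVA, or only to secondary outcomes. This also stands. It rules out the tempting claim that no outcome in the aim has 80% power under the plan's own adjustment. Bonferroni and a common effect are assumptions made here. Even at alpha 0.05/3, a true effect of (2.394 + 0.842) × √(2/54) = 0.62 SD would have 80% power, and no passage excludes an effect of that size.

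Two other readings fail. Counting four outcomes at three visits as twelve separate chances of success, or quoting power for twelve tests, matches no analysis that the protocol states. Reading 0.74 as a variance, which would need 73 per arm, contradicts both the legend's own words and the resulting 54.

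Finally, an article condenses a fuller protocol, and an analysis plan that is not shown may define the family and method. That excuses the missing multiplicity detail. It does not excuse a calculation that the article prints in full for an outcome it does not identify, or an effect measure that differs from the one used for sizing.

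**Conclusion.** The point holds in a limited form. The sample size is arithmetically sound for one outcome with a true effect of 0.54 SD tested alone at two-sided 5% (80.2% with 54 evaluable per arm). The 80% cannot be assigned to any outcome in the protocol, because no primary outcome, unit or time point is named and the aim covers at least three outcomes.

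If the promised adjustment covers those outcomes, power at that effect is about 66% for three or 62% for four, under the assumptions in step 4 of the working. Baseline adjustment could recover some or, at an assumed correlation of 0.5, about all of the loss for three outcomes. The conflict between sizing on means and reporting proportions is a separate inconsistency in the text and needs no assumption. The legend error is cosmetic.

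The matter still needs repair before the data are analysed, because it decides which result the trial may claim as confirmatory.

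**What to change.** 1. Name one primary outcome and one time point in the Aim, Sample size and Study outcomes sections, and state the unit and the source of 0.74 and 0.40 for that outcome.
2. Test it at two-sided 0.05 as a difference in means.
3. Place the other outcomes of the aim in a secondary family controlled by a fixed sequence or by Holm's method, and say which comparisons the adjustment covers.
4. Reconcile the Statistical analysis section's difference in proportions with the difference in means used for sizing.
5. Correct the legend so that σ is the SD and δ the difference.

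If several outcomes remain primary, define the family and the success rule, and restate the power with its assumptions. Where success on any one suffices, that means power at the adjusted alpha.

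The cost is protocol and analysis plan wording and a registry update. No extra participants are needed. The downside is that the stated power may become less favourable, either because the named outcome has a different SD or because alpha is shared.
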